### Analysis

We will compare the proportion with microbial cure at 4 weeks between arms using the Chi square test, and 95% confidence intervals for the difference between proportions reported. While randomisation should ensure balance of baseline characteristics, if there are meaningful differences in baseline characteristics including sexual behaviour, a multivariable logistic regression analysis will be undertaken to adjust for these factors.

#### Primary analysis

Our primary analysis will be a modified intention to treat analysis (m-ITT) including only those who commenced randomised therapy at recruitment (at least one dose) and those who provided a rectal specimen for chlamydia testing at week 4.

#### Secondary analysis

We will undertake two per protocol analyses in which participants who took less than 10 doses of their allocated treatment [28] or vomited within 1 h of any dose will be excluded: i) an analysis of the primary outcome of the microbial cure, and; ii) an analysis of the secondary outcome of microbial cure in which cases classified as new infection or a false diagnosis are grouped with microbial cure to create a binary variable for the analysis (microbial cure [including new infection and false positive cases] vs treatment failure).

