#### Exclusion criteria

Men will be excluded if they: i) report use of antibiotics for other purposes in the last 2 weeks; ii) have a known contraindication to the use of azithromycin or doxycycline including allergy; iii) present with symptomatic proctitis. Because MSM will be recruited at clinical services, it will not be possible to genotype their infections to detect LGV at recruitment. LGV genotyping will take place at the conclusion of the trial. Men who are randomised and subsequently found to have asymptomatic LGV based on genotyping at the conclusion of the trial, estimated to be <6% of the trial population [31] will be excluded from our analysis as LGV requires more prolonged doxycycline treatment for cure [32]. The sample size will account for this – see *Sample Size*.

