### Intervention

Participants will be randomly allocated to one of the following treatment groups:

Azithromycin: Participants will receive 1 g of active azithromycin (500 mg tablets × 2), plus 13 placebo doxycycline tablets, identical in appearance to the active azithromycin. Participants will be required to take the two azithromycin tablets under observation at time of recruitment and then advised to take a single placebo tablet morning and night for the next 7 days;

Doxycycline: Participants will receive 14 active doxycycline tablets (100 mg), plus one placebo azithromycin tablet, all identical in appearance to active azithromycin. Participants will be required to take one active doxycycline and one placebo azithromycin tablets under observation at time of recruitment and then advised to take a single active doxycycline tablet morning and night for the next 7 days.

Participants will be advised to take the drugs with food to minimize gastrointestinal side effects and to minimize sun exposure or use sun screen to reduce the risk of photosensitivity.

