### Outcomes

#### Primary outcome

Treatment efficacy measured as microbial cure defined as a negative chlamydia NAAT test result performed on a self-collected rectal swab at week 4.

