#### Weekly data collection

Participants will be asked to respond to a weekly short message service (SMS) that collects (via online link) whether they had: any receptive anal sex in the last week; sex with any new sexual partners; sex without a condom in the last week; used any douching and/or intra-rectal devices; any anogenital symptoms; any chlamydia testing elsewhere; taken any further antibiotics.

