#### Side effect reporting

During the first week, participants will also be asked daily via SMS whether they had any diarrhoea or vomiting that could impact on their levels of antibiotic absorption.

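### The per-protocol exclusions omit non-study antibiotics and retreatment before week 4, so a man cleared by another drug counts as a cure of his allocated arm

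*Protocol article*

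**What the plan says.** All places are in the protocol article.

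- **Primary outcome.** Cure is a "negative chlamydia NAAT test result performed on a self-collected rectal swab at week 4". No condition on other treatment is attached.
- **Primary analysis.** The modified intention-to-treat (m-ITT) set is defined as "including only those who commenced randomised therapy at recruitment (at least one dose) and those who provided a rectal specimen" for testing at week 4.
- **Secondary analysis.** Both per-protocol analyses use the same rule: they exclude men who "took less than 10 doses of their allocated treatment" and men who vomited within an hour of any dose. The only other analysis exclusion in the article is for LGV, under Exclusion criteria.
- **Exclusion criteria.** Men who "report use of antibiotics for other purposes in the last 2 weeks" cannot enter.
- **Weekly data collection.** The SMS link asks about "any chlamydia testing elsewhere; taken any further antibiotics". Table 1 places the other-medications item on Days 7, 14 and 21. The section on the 4-week follow-up adds STI diagnoses, checked against the medical record.
- **Side effect reporting.** In the first week men are asked each day "whether they had any diarrhoea or vomiting that could impact on their levels of antibiotic absorption". Table 1 marks adverse drug reactions under Days 2-6 only.
- **Intervention.** In the azithromycin arm, "Participants will be required to take the two azithromycin tablets under observation at time of recruitment". Every later tablet in that arm is placebo.

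**The concern.** A per-protocol analysis is meant to show what the allocated drug does when taken as planned. The article treats outside antibiotics as disqualifying just before entry and takes the trouble to record them afterwards, but no stated analysis rule uses the follow-up record. A man whose infection was cleared by another drug is kept, and his negative swab is credited to the trial drug.

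The secondary-outcome algorithm cannot pick him up, because sequencing and mRNA testing apply only to men who are NAAT-positive at week 4. He is therefore a cure in the m-ITT analysis and in both per-protocol analyses.

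If failures are cleared at the same rate in both arms, the arm with more failures gains more borrowed cures and the difference shrinks. That works against the hypothesis that doxycycline is superior. If retreatment falls mainly on azithromycin failures, the shrinkage is larger.

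A smaller matter is that the other per-protocol rule, vomiting within an hour of a dose, has no matching data item described, least of all for Day 1.

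**Working it through.** **Inputs from Sample size and Table 2.** Cure 98% (doxycycline) against 93% (azithromycin); 700 men, 1:1; 14% lost and 6% LGV; 5% significance. Two-sided testing is my assumption, as it reproduces the table.

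**Reproducing the plan's figure.** With pooled variance and no continuity correction,

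n per arm = [1.960·√(2p̄q̄) + 0.842·√(p₁q₁ + p₂q₂)]² / d².

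Here p̄ = 0.955, so 2p̄q̄ = 0.08595; p₁q₁ + p₂q₂ = 0.0196 + 0.0651 = 0.0847; d = 0.05. This gives 269 per arm, 538 in total, as in Table 2. The effective size is 700 × (1 − 0.14 − 0.06) = 560, or 280 per arm, and power there is 81.6%. The plan's arithmetic is not in question.

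**Model A: a share s of failures in each arm is cleared by another drug (s is assumed).** Observed failure = f(1 − s), with f = 2% and 7%.

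| s | Doxycycline failure | Azithromycin failure | Difference (points) | Power, 280 per arm |
|---|---|---|---|---|
| 0 | 2.0% | 7.0% | 5.0 | 81.6% |
| 10% | 1.8% | 6.3% | 4.5 | 77.2% |
| 20% | 1.6% | 5.6% | 4.0 | 72.0% |
| 30% | 1.4% | 4.9% | 3.5 | 66.0% |

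Few men are involved. Expected azithromycin failures are 280 × 0.07 = 19.6, so 10% to 30% is about 2 to 6 men. If only azithromycin failures are cleared, 10% gives 4.3 points (power 72.4%) and 20% gives 3.6 points (60.6%).

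**Does excluding these men repair it?** Under Model A they leave both numerator and denominator, so failure becomes f(1 − s)/(1 − fs):

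| s | Doxycycline | Azithromycin | Difference (points) |
|---|---|---|---|
| 10% | 1.8/99.8 | 6.3/99.3 | 4.54 |
| 20% | 1.6/99.6 | 5.6/98.6 | 4.07 |
| 30% | 1.4/99.4 | 4.9/97.9 | 3.60 |

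Exclusion recovers almost nothing. Counting these men as not cured returns failure to 2% and 7%, and the difference to 5 points.

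**Model B: antibiotic use is unrelated to failure.** Suppose 10% of all men in both arms take a drug that clears any failure. Left in, they give 98.2% against 93.7% cure, 4.5 points, power 77.2%. Excluded, the 5-point difference is restored, with power 77.4% on the smaller set. Here exclusion corrects the estimate but not the power.

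The two mechanisms therefore need two remedies: exclusion for incidental antibiotics, and a not-cured classification for retreated infection.

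**Vomiting, passages side by side.** Secondary analysis needs vomiting timed to within an hour of any dose. Side effect reporting describes a daily question throughout the first week, without timing to a dose. Table 1 shows Days 2-6. Intervention puts all active azithromycin on Day 1. No described item is tied to vomiting after that dose.

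**The case against.** **The m-ITT handling is ordinary treatment policy.** This stands. Analysing the week-4 result whatever else was taken is defensible, and the m-ITT should not be redefined. The gap lies in the per-protocol rule, which the article spells out and which omits contamination.

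**Details may sit in a full protocol or SAP.** This stands in part. Concomitant-medication handling often does. But the per-protocol exclusions are fixed in the text as a closed pair, and as written they keep these men.

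**The range is assumed and may be high.** This stands. Men are asymptomatic at entry, blinded, and due a test at Day 28, so early retesting and retreatment may be rare.

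**Excluding retreated failures hardly helps and depends on outcome.** This stands, as shown above. It is why exclusion alone is not enough.

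**The data may not suffice.** This stands in part. The other-medications item stops at Day 21, no agent is mentioned, and the week-4 questionnaire as described lists STI diagnoses but not antibiotics.

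A reader might go further in three ways that the article does not support:

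- *That the vomiting gap credits other drugs' cures to azithromycin.* A man who vomited his active dose and stays in would tend to add a failure to that arm.
- *That the vomiting rule cannot be applied on Day 1.* The rule covers any dose, a nurse observes the first one, and a Day 2 message could look back. The article shows only that no such item is described.
- *That the 10-dose rule should count active tablets only in the azithromycin arm.* It is true that the rule can drop azithromycin men who missed only placebo. But one tablet count for both arms is what a blinded double-dummy design permits. Counting active doses only would keep nearly all azithromycin men while selecting adherent doxycycline men.

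**Conclusion.** The point holds for the per-protocol analyses. As written, they keep men exposed to other anti-chlamydial antibiotics or retreated before week 4 and, if NAAT-negative, count them as cures of the allocated arm, although the article regards such exposure as disqualifying at entry and records much of it afterwards. The m-ITT analysis is not in error, but it would benefit from a sensitivity analysis.

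The likely direction is towards no difference. The size is unknown. The figures of 4.5 to 3.5 points and 77% to 66% power rest on the plan's 98% and 93% cure, 280 men per arm, and an assumed 10% to 30% of failures cleared equally in both arms. They do not show that the primary conclusion is at risk. Baseline power is only slightly above 80%, however, so even a few such men take it below the target.

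The vomiting passages are a separate inconsistency of data capture.

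**What to change.** 1. **Per-protocol exclusions.** Add any non-study antibiotic with anti-chlamydial activity taken before the week-4 swab, judged blind to arm against a list fixed in advance. Record the agent and date, and let the week-4 questionnaire cover Days 22-28.
2. **Sensitivity analysis of the m-ITT.** Keep the m-ITT as primary. Add one analysis in which men diagnosed with rectal chlamydia and retreated before week 4 count as not cured. Report the number of such men by arm.
3. **Vomiting.** Reconcile Secondary analysis, Side effect reporting and Table 1, so that vomiting is recorded in relation to a dose and the Day 1 dose is covered.

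The cost is analysis wording, a short blinded adjudication, and a small change to the questionnaire and SMS items. The per-protocol set becomes slightly smaller. Most of the variables are already collected, and treatment and follow-up do not change.

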**Methods/Design:**

The Rectal Treatment Study will recruit 700 MSM attending Australian sexual health clinics for the treatment of rectal chlamydia. Participants will be asked to provide rectal swabs and will be randomised to either azithromycin 1 g single dose or doxycycline 100 mg twice daily for 7 days. Participants will be asked to complete questionnaires about adverse drug reactions, sexual behaviour and drug adherence via short message service and online survey. The primary outcome is the treatment efficacy as determined by a negative chlamydia nucleic acid amplification test at 4 weeks post treatment. Secondary outcomes will utilise whole genome sequencing and mRNA assay to differentiate between treatment failure, reinfection or false positive results.

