**Fig. 1 Fig1:**
[figure not shown]
Outline of trial schema. Follow up at 4 weeks post recruitment

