A repeat positive chlamydia test at follow up does not necessarily indicate treatment failure; it could be a re-infection or a false positive result. A strength of this trial is that we can take advantage of the latest technology to more accurately discriminate between treatment failure and re-infection or false positive result. We will use WGS to differentiate between new infection and treatment failure. WGS is the most discriminatory tool available as it can identify conclusively whether the specific strain at follow up is different from that at recruitment thereby indicating a new infection. Previously, studies have used O*mpA* genotyping or multi-locus sequence typing (MLST) to characterise the genovar [44], but these techniques are considerably less discriminatory than WGS. We will use mRNA tests to identify false positive cases. Standard chlamydia tests detect chlamydia nucleic acid which includes both viable and non-viable (dead) organisms. When antibiotic treatment kills chlamydia, it can take 3 weeks to clear the nucleic acid from the genital tract [59], so any NAAT conducted during this time may detect non-viable organism only and be a false positive. Chlamydial mRNA assays use a quantitative real-time chlamydia molecular test (see p7) and will quantitatively measure mRNA transcription of omp2 (omcB) outer membrane protein in chlamydia as an expression of viable organisms (active infection) [37]. In addition, we will collect comprehensive sexual practice data to identify men at risk of re-infection using SMS.

This trial must be done to ensure STI management guidelines internationally are evidence-based and recommend the most efficacious treatment for rectal chlamydia so that ongoing transmission is minimised.

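### The outcome corrected by sequencing and mRNA testing is planned only in the per-protocol set; an m-ITT version should come first, and the timing of the week-4 test should be worded consistently

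*Protocol article*

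**What the plan says.** The Primary outcome is "a negative chlamydia NAAT test result performed on a self-collected rectal swab at week 4", with no correction for reinfection or residual nucleic acid. Its analysis set is given under Primary analysis: "Our primary analysis will be a modified intention to treat analysis (m-ITT) including only those who commenced randomised therapy at recruitment" and who also gave a rectal specimen at week 4.

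The Secondary analysis section then states: "We will undertake two per protocol analyses in which participants who took less than 10 doses of their allocated treatment" or vomited within an hour of any dose are left out. The first of the two repeats the primary outcome in that reduced set. The second is "an analysis of the secondary outcome of microbial cure in which cases classified as new infection or a false diagnosis are grouped" with cure, giving a binary contrast with treatment failure. No other comparison in the article uses the sequencing and mRNA classification.

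The Secondary outcomes section applies that classification to every man who is positive at week 4, whatever his adherence. It also relies on the randomised design to spread new infections and false positives evenly across arms.

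On timing, the Abstract describes the outcome as "a negative chlamydia nucleic acid amplification test at 4 weeks post treatment". The Fig. 1 legend says "Follow up at 4 weeks post recruitment", and Table 1 places the visit at Day 28. The Discussion says of dead organisms that "it can take 3 weeks to clear the nucleic acid from the genital tract".

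**The concern.** The Discussion presents the ability to separate treatment failure from reinfection and false positives as a strength of the trial. On the stated plan that ability is used only after men have been removed for events that follow randomisation.

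The removal need not be neutral between arms. The protocol itself says that poor adherence to the 7-day course can raise the risk of treatment failure (Background) and could affect efficacy (Study design and setting). An under-dosed doxycycline man has missed active drug. An azithromycin man below the same tablet count has usually missed only placebo. The exclusion can therefore flatter the arm that the trial hypothesises to be superior.

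The m-ITT comparison, which avoids this exclusion, has no corrected version. Because the two regimens end about a week apart, the statement that false positives will be evenly distributed is also not secured by randomisation. Randomisation balances the men, not the consequences of regimen length.

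**Working it through.** **1. The planned analyses side by side**

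| Analysis set | Uncorrected week-4 NAAT | Corrected outcome |
|---|---|---|
| m-ITT | Planned (primary) | Not stated |
| Per protocol | Planned (secondary, i) | Planned (secondary, ii) |

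One of the four cells is empty. It is the one that combines the better outcome definition with the less selected set.

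**2. What the per-protocol rule removes** (inputs from the Intervention section)

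- Azithromycin arm: 2 active tablets, both observed on Day 1, then 13 placebo tablets. The 10-dose threshold can be applied here only by counting placebo, so a man below it has still had all his active drug.
- Doxycycline arm: 14 active tablets, 1 of them observed, so 14 − 1 = 13 are unsupervised. A man below 10 doses has missed active drug.
- The vomiting rule can also remove azithromycin men who lost active drug after the observed dose. This works in the opposite direction, so the exclusion falls mostly, but not only, on placebo-missers in that arm.

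**3. Illustration of size** (all rates assumed; the documents give none)

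Let f be the fraction of doxycycline men under 10 doses, a their failure rate and b the failure rate of the rest. Failure with everyone kept is f·a + (1 − f)·b. Per protocol it is b. The understatement is f·(a − b). With a = 10% and b = 1%:

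| f | All kept | Per protocol | Understatement |
|---|---|---|---|
| 5% | 0.05×0.10 + 0.95×0.01 = 1.45% | 1.0% | 0.45 points |
| 15% | 0.15×0.10 + 0.85×0.01 = 2.35% | 1.0% | 1.35 points |
| 20% | 0.20×0.10 + 0.80×0.01 = 2.80% | 1.0% | 1.8 points |

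If a = b the understatement is zero. In the azithromycin arm, dropping men who missed only placebo leaves the expected failure rate unchanged, provided that missing placebo is unrelated to failure. For scale, the design difference is 98% − 93% = 5 points.

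**4. Interval from last active dose to the Day-28 test**

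- Azithromycin: last active dose on Day 1; 28 − 1 = 27 days.
- Doxycycline: 13 tablets remain after the observed one, taken twice daily. Starting on the evening of Day 1 they end on Day 7; starting on the morning of Day 2 they end on Day 8. That gives 28 − 7 = 21 or 28 − 8 = 20 days.
- Gap between arms: 27 − 21 = 6 to 27 − 20 = 7 days.

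Counted from the last dose, the doxycycline interval sits at the 3-week clearance time that the Discussion mentions, and the azithromycin interval is about a week past it. Neither arm is tested 4 weeks after a completed 7-day course, so the Abstract wording does not match Fig. 1 or Table 1 for doxycycline.

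**5. The sample size is not in dispute**

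A two-sided 5% test of two proportions with pooled variance, for 98% against 93% at 80% power, gives 538 in total, as in Table 2. The effective size is 700 × (1 − 0.14 − 0.06) = 560. Adding an m-ITT analysis of the corrected outcome changes neither.

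**The case against.** The strongest reply is that the plan already holds three analyses. The primary against the first per-protocol analysis shows the effect of changing the set. The first against the second per-protocol analysis shows the effect of changing the outcome definition. A reader might infer that the two effects cannot be told apart; that is too strong. What the three analyses cannot show is how the correction acts on the men the per-protocol rule excludes. This is a gap in completeness, not a fault in the primary analysis.

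The m-ITT set is also not the full randomised set. It requires a dose and a week-4 specimen, and LGV cases are excluded. The corrected outcome has its own admitted weakness: a man positive with the same organism is called newly infected, and so grouped with cure, if he reports unprotected receptive anal sex. An m-ITT version would carry that too. These objections stand; they limit what the added analysis can claim but do not favour the per-protocol set.

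Three stronger readings are tempting and are not supported:

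- *That residual-nucleic-acid positives do fall preferentially on doxycycline.* The Discussion starts the 3-week clock when the organism is killed, not at the last dose, and doxycycline also begins on Day 1. The 3 weeks is a time clearance can take, stated for the genital tract. A difference between arms is possible but not shown. It would count against doxycycline, so it could not produce a false superiority claim. For reinfection, blinding and matched tablet schedules support balance.
- *That such positives cost the trial a calculable amount of power.* The 98% in the Sample size section is microbial cure at 4 weeks, and cure is defined as a negative NAAT. Residual positives are already inside that rate, so subtracting them again would count them twice.
- *That swabs taken within 21 days of the last active dose should be excluded as a check.* With intervals of about 20–21 and 27 days, this would remove most on-schedule doxycycline men and almost no azithromycin men. It would repeat the arm-dependent, post-randomisation selection criticised here.

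**Conclusion.** The point holds in a limited form. The article does not leave the analysis set for the corrected outcome open: it assigns it to the per-protocol set and states no m-ITT version. That set excludes men after randomisation by a rule that bears on active drug in one arm and mostly on placebo in the other, so it may favour doxycycline. The understatement of doxycycline failure runs from nothing to 1.8 points over the assumed range; actual adherence and failure rates are unknown. The conclusion rests on the protocol's own premise that under-dosing of doxycycline can raise failure.

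The 6–7 day difference in interval is a reason not to take the even distribution of false positives as guaranteed. It is not evidence of bias. The discrepancy between post treatment and post recruitment is a plain inconsistency. The primary analysis and the sample size are unaffected. The change is worth making because it is cheap and puts the trial's distinctive laboratory work into its less selected comparison.

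**What to change.** 1. In Secondary analysis, state that the corrected outcome (treatment failure against cure, new infection or false positive) is analysed first in the m-ITT set, with the per-protocol version as supportive. Tabulating the classification categories by arm in the m-ITT set would also show directly whether false positives are balanced.
2. In Secondary outcomes, soften the statement on even distribution: randomisation does not guarantee it for false positives that depend on when treatment ended.
3. Reconcile the Abstract with Fig. 1 and Table 1 on the reference point for the 4-week test.

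The cost is one extra secondary analysis and two wording changes. No further swabs or assays are needed, because every week-4 positive is already to be classified regardless of adherence. The added analysis still carries the acknowledged misclassification of same-strain positives, and its report should say so.
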